**Methods/designs:**

The study outlined in this protocol will assess and compare the influence of the two programs on various aspects of maternal health care including trends in program uptake, institutional delivery rates, maternal and neonatal outcomes, quality of care, experiences of service providers and users, and cost effectiveness. The study will collect primary data using a combination of qualitative and quantitative methods, including facility level questionnaires, observations, a population based survey, in-depth interviews, and focus group discussions. Primary data will be collected in three districts of each province. The research will take place at three levels: the state health departments, obstetric facilities in the districts and among recently delivered mothers in the community.

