Using the platform of the NRHM, the government introduced demand-side financing initiatives for maternal health to reduce financial barriers that often preclude women from accessing skilled attendance at birth [8]. Two large scale demand-side financing programs to promote institutional delivery, conditional cash transfers (CCT) and vouchers, are currently in operation. The intended outcome of both programs is to promote institutional delivery, thus reducing maternal mortality through improving access to EmOC.

A traditional CCT provides a monetary incentive directly to the intended group on the condition the beneficiary satisfies a pre-defined set of requirements [9]. India’s Janani Suraksha Yojana (JSY or Safe motherhood program), a nationwide program, is a conditional cash transfer to all women who deliver in public sector institutions. This program will be studied in Madhya Pradesh Province. Chiranjeevi Yojana (CY or Long life program) is operational only in the Gujarat province, and functions in the context of an existing strong private obstetric care sector. It is a voucher based system where private obstetricians are reimbursed by the government to perform deliveries of tribal women or those living below the poverty line. Vouchers, which tend to be cashless, are used to reduce the direct costs of healthcare and increase demand for services [10] (Table 1).

**Table 1 T1:** Characteristics of two Indian demand-side financing programs for maternal health

	** *CY – a voucher program (Gujarat)* **	** *JSY – a conditional cash transfer (MP)* **
** *Area of Operation* **	Gujarat (60.4 million)	Nationwide (studied here in Madhya Pradesh) (72.6 million)
** *Context* **	Socioeconomically relatively advanced: MMR half of that in MP (142/100 000), 16% population below the poverty line	Poor socioeconomic indicators, MMR (310/100 000), largely rural province, 38% of the population below the poverty line
** *Target group* **	Mothers below poverty line and tribal mothers	All mothers
** *Type of Program* **	Payment by state **to the private provider i.e. obstetrician***(voucher based)*	CCT – payment by state to **the mother***(conditional cash transfer)*
** *Incentive for* **	Institutional delivery	Institutional delivery
** *Accepted place of delivery* **	Empanelled private sector obstetric facilities	Public sector institutions largely
** *Involvement of private sector* **	Yes	Yes (extremely restricted)

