## Methods

### Setting

The study will take place in two provinces (Figure 1) where the demand-side financing programs are operational, Madhya Pradesh and Gujarat. These provinces differ from one another both socio economically and with regard to other health related indicators (Table 3).

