**Figure 1 F1:**
[figure not shown]
MATIND Study Area: Selected Study Districts in Madhya Pradesh and Gujarat.

**Table 3 T3:** Demographic and maternal health indicators of Gujarat, Madhya Pradesh

	**Population**	**Administrative districts**	**BPL**	**Literacy rate**	**Institutional delivery**	**IMR**	**MMR**
Madhya Pradesh	72.6[25]	50	38%[26]	71%[25]	47%[27]	62[28]	310[29]
Gujarat	60.4[30]	25	16%[31]	79%[32]	56%[33]	44[28]	142[28]

For studies at the district level, we purposefully selected three districts from each province in collaboration with the provincial ministries of health. The selected districts include districts from different geographic areas of each province, varying human development indices and represent different population sub groups including disadvantaged groups like scheduled castes (SC) and tribes (ST).

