A quantitative retrospective data analysis will be completed with data ascertained from call centers to determine utilization patterns and uptake of the respective transport systems. Socio-demographic characteristics of the beneficiaries and other outcomes will be collected in a cross-sectional questionnaire to study equity in use of the service.

NRHM program officials and District Chief Medical & Health Officers (CMHOs) will be interviewed to gain insight into the structure under each model and the benefits and limitations of the respective decentralized and centralized emergency transportation services. The discussion will include perceptions on efficiency, geographical accessibility, functionality, sustainability, technical capacity, constraints and motivations of the human resources, and procedural limitations. In addition, costs associated with implementation and ongoing usage will be elicited.

All interviews will be conducted in Hindi by a research assistant, transcribed and then translated into English. In-depth interview data will be analyzed thematically, using the framework approach. The analysis will draw out differences between the two schemes in terms of implementation, stakeholder views of the schemes and experiences of utilization. A cost effectiveness analysis between the two programs is also planned.

A cost effectiveness of the two programs (objective iv) will be performed through two different methods. The first approach will be to compare the costs and outcomes of the two programs for matched groups of participants. The primary outcome will be the proportion of institutional delivery. Other outcomes to be analyzed will be the proportion of cesarean deliveries, antenatal check-ups and delivery outcomes (live births, stillbirths, miscarriages). The costs will primarily be from the payer perspective, the state, but also costs to the patients will be collected and analyzed. The second approach will be to analyze each system separately from an equity perspective, i.e. how costs and access to services are distributed according to categories of socio-economic status. In view of the complexity and multi-dimensionality of both the interventions and the outcomes, we will not aim to comprise the analysis in a single index number.

2. Facility Level:

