At the facility level we will collect primary data on the types of facilities that are administering obstetric care under the programs (objective v), and the quality of care received (objective vi). These facilities will be visited to study maternal health outcomes. Both quantitative and qualitative methods will be utilized to achieve these objectives.

An initial list of all public and private facilities in the study districts will be obtained from government records. The list will be verified by site visits. Snowballing will then be utilized to identify any missing private facilities where obstetric care is provided. A modified Averting Maternal Death and Disability (AMDD) survey [12] will be administered to each facility by a member of the research team and the performance of EmOC functions will be ascertained by interviewing key staff. The facilities will be classified with reference to standards based on the UN and WHO definitions [13] as non-EmOC, Basic Emergency Obstetric Care (BEmOC) or Comprehensive Emergency Obstetric Care (CEmOC). The availability level of EmOC services will be ascertained with reference to the population; the number of CEmOC, BEmOC and non-EmOC facilities in the public and private sector and in the rural and urban areas will be calculated.

A cross-sectional survey will provide additional information on how the facilities function under the respective programs as well as aspects of quality of care provided. The assessment will include variables on infrastructure, accessibility, human resources, functional equipment, accessibility to drugs and supplies, referral communications and processes, infection control procedures and service statistics. This survey will provide the current operating state of the facilities. Descriptive statistics will be calculated for the areas mentioned above. These will be compared between public and private facilities and between the two programs.

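### The matched JSY-versus-CY cost-effectiveness comparison cannot separate program from province, and its primary outcome is 100% by definition among participants

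*Protocol article*

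**What the plan says.** The abstract sets the overall aim to "assess and compare the influence of the two programs on various aspects of maternal health care". Under Data collection methods, provincial level, objective iv has two approaches. The first reads: "The first approach will be to compare the costs and outcomes of the two programs for matched groups of participants". For this, "The primary outcome will be the proportion of institutional delivery". Caesarean deliveries, antenatal check-ups and delivery outcomes are further outcomes, and costs are taken mainly from the state's side. The second approach looks at each system on its own from an equity angle.

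On where each program is observed, the Background says of JSY: "This program will be studied in Madhya Pradesh Province". Of the voucher program it says: "Chiranjeevi Yojana (CY or Long life program) is operational only in the Gujarat province". Within each province, "we purposefully selected three districts from each province in collaboration with the provincial ministries of health". The Setting section acknowledges that "These provinces differ from one another both socio economically and with regard to other health related indicators".

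The community-level text (objective vii) defines participation. For JSY it is delivery in a public facility. For CY it is delivery in an approved facility by a mother who is tribal or below the poverty line (BPL). The same section plans propensity score matching of program users to non-users.

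**The concern.** A comparison of matched participants looks like an adjusted estimate of one program against the other. Here every JSY participant lives in one province and every CY participant in another. Background obstetric risk, local prices and the private obstetric supply that existed before the program go with the province. A difference in caesareans, stillbirths or cost per delivery could therefore arise with no difference between cash transfer and voucher. The Discussion addresses the results to policy makers who run or consider such programs, so the limit on this contrast needs to be stated.

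The primary outcome raises a second problem. If the groups compared are program participants, the outcome is fixed by the way they were selected.

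**Working it through.** The article gives no sample size, power or effect size for this comparison, so there is no figure to reproduce. The check is one of identification and definition.

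**1. Can program be separated from province?** Let P = 1 for Gujarat and 0 for Madhya Pradesh, T = 1 for CY and 0 for JSY, and x = maternal characteristics. The model is

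E[Y] = a + bP + cT + d'x.

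Because T = P for every participant, this reduces to a + (b + c)P + d'x. Only the sum b + c (province plus program) can be estimated.

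- Six districts, three per province, with columns for intercept, province and program: rank 2 of 3.
- The same columns with three individual covariates added: rank 5 of 6.

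Covariates add rank for themselves but never separate P from T. Matching on x has the same limit, and no sample size changes it.

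**2. What can the primary outcome show among participants?**

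- JSY participants all delivered in a public facility, so the proportion is n/n = 100%.
- CY participants all delivered in an approved facility, so the proportion is n/n = 100%.
- Difference: 100% − 100% = 0, whatever the programs do. A cost per additional institutional delivery would have a zero denominator.

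Comparing participants with non-participants does not repair this outcome. Participants are at 100% by definition. JSY non-participants delivered at home or in a private facility, and CY non-participants anywhere outside an approved facility. The gap reflects the definitions.

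**3. Do the settings differ?** From Tables 1 and 3, Madhya Pradesh v Gujarat:

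- MMR 310 v 142: 310/142 = 2.18
- IMR 62 v 44: 62/44 = 1.41
- BPL 38% v 16%: 38 − 16 = 22 points

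None of these is an outcome of objective iv. They show that the settings are unlike, not how far the contrast would be biased.

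**4. Is there a safeguard elsewhere?** The propensity matching, in both the community-level text and the Discussion, is users against non-users, which is a different contrast. The refusal to reduce the analysis to one index number is justified by complexity and does not address attribution.

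**The case against.** The strongest reply is that this is a condensed article and its sentence does not say that JSY mothers are paired with CY mothers. The only matching it specifies is users against non-users. The Discussion names two measures of impact, mortality estimates and beneficiaries against non-beneficiaries, and a raw JSY-CY contrast is neither. The second economic approach takes each system separately. This stands in part: most of the analysis needed is already planned, and nowhere does the article attribute a provincial difference to program type. A reader might infer that it will, but that is a prediction. Still, the sentence does compare the two programs, in contrast to the separate analyses that follow, and nothing limits what may be concluded.

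Three further replies hold:

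- Delivery sector and emergency transport appear in Table 1 as features of the programs, so they are at least partly what is being compared and not simply confounders. Background risk, prices and pre-existing private supply remain.
- The difference in target groups could be handled by restriction or matching on BPL or tribal status.
- The facility comparison ("These will be compared between public and private facilities and between the two programs") concerns descriptive statistics and needs no change on this ground.

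If participants meant everyone surveyed, the 100% problem would disappear but the confounding would not. The matching paragraph uses the word for program users.

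A stronger reading is also tempting: that the 9-point gap in institutional delivery in Table 3 (56% − 47%) would appear as a spurious program effect. The documents do not support it. That gap cannot arise between two groups that are both at 100%, and the provincial figures may already contain program effects.

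**Conclusion.** The point holds for the direct JSY-CY contrast in the first approach of objective iv. Program and province are completely confounded there, and maternal matching cannot undo it. Among program participants the stated primary outcome is uninformative by definition. The first result needs only one province per program. The second rests on reading participants as program users.

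No size can be put on the bias from the article. A reader might also infer that the whole evaluation is confounded with province. It is not: the user/non-user matching and the separate equity analyses avoid this problem if done within province.

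**What to change.** In objective iv, replace the direct matched contrast with within-province estimates for each program:

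- **Institutional delivery:** use all eligible women as denominator, or the district time series already planned under objective i, and not participants against non-participants. A single survey of eligible women gives a level; only the time series shows change.
- **Costs and other outcomes:** use the propensity-matched beneficiaries and eligible non-beneficiaries of objective vii, matched within province.
- **Presentation:** show the two within-province results side by side, with Madhya Pradesh also shown for BPL or tribal mothers where that status is recorded. The article does not name it among the items collected there, so this should be confirmed.
- **Interpretation:** state that any direct JSY-CY difference is descriptive and is not attributed to program type.

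The cost is wording and analysis, since the survey already covers non-participants, costs and socio-demographic details in both provinces. The between-program claim becomes weaker, and the restricted Madhya Pradesh subset is smaller. Selection into participation within each province, and the different make-up of non-participants in the two programs, remain and should be listed as limitations.

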With regard to the JSY program in MP, to explore the reasons for the decision to subsequently reduce the role of the private sector in the program. Also to explore among selected erstwhile participating private facilities, their experience with JSY and their perception on the state decision to exclude them from the scheme.

With regard to the CY program, to explore experiences and motivations among selected private providers currently participating in the program, reasons for non-participation among a sample of those who were eligible but never participated and those who participated initially but have since left the program.

(iii) Emergency transportation for obstetric care: To study two different emergency obstetric transportation models utilized in each of the programs with regards to coverage, equity in access, current utilization, and cost of the service. Further, to explore among a group of mothers their experience of gaining access to and using the transportation.

(iv) Cost-effectiveness of the Programs: To develop and apply a model for assessment of the utility of the two maternal health programs and to perform a sensitivity analysis by testing alternative assumptions for a cost utility analysis.

2. Facility Level (public and private facilities):

(v) Facility Survey: To list all facilities in the study districts offering obstetric care and classify them as non-EmOC, basic or comprehensive emergency obstetric care (BEmOC or CEmOC) facilities. Further, to study the characteristics of these facilities with regard to ownership, accessibility, bed strength, human resources, training, referral communications and processes, availability of equipment, drugs and supplies and infection control procedures.

(vi) Quality of Care: To study in EmOC facilities the quality of care through direct observation of normal deliveries, a review of case records and registers and assessments of provider competence. Further to study experiences and perceptions of quality of care of mothers who delivered under the respective programs, and to study key procedures they experienced. In cases of mothers who were referred into facilities, referral indications and transportation details will be studied.

3. Community level (mothers in sampled study villages):

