#### Data collection methods

1. Provincial (policy) level:

At this level we will collect secondary data on program related inputs, outputs and outcomes in each province. A time series analysis, consultations with key stakeholders, and review of relevant program documents will allow us to study program trends (objective i) and comment on the uptake of the programs since inception. A complete time series will be derived from maternal health data with regard to uptake (proportion of eligible women who participate), institutional delivery (total number of women delivering in a public or private facility), district level ante-natal care (ANC) coverage (proportion of women completing >3 ANC visits), and maternal and neonatal deaths. The data will be obtained from multiple sources including the District Level Household Survey (DLHS), Annual Health Survey, Sample Registration System (SRS), Vital Registration and health department sources for the purpose of data triangulation and the development of robust estimates. A major challenge in the analysis is the lack of complete time series for the maternal mortality data. Instead of relying on a single source for information, statistical data fusion techniques will be applied to collate data from various sources. The data fusion techniques will borrow strengths across time and space from the existing data to derive a complete time series estimates for the variables of interest.

A second study at the policy level will focus on trends in private sector participation (objective ii) in each of the programs over time. The role of private providers varies in each program. Private providers played a small part in the JSY program; however they are a large resource in Gujarat and thus the central focus in CY. Private facility characteristics will be studied through a cross-sectional facility review (see objective v). In MP, we will explore with NRHM program managers the experiences of collaborating with private providers and the perception of the role of the private sector in JSY, justification for criteria used for selection, and rationale for their inclusion in and subsequent exclusion from the program through in-depth interviews. Implementation issues and the overall benefits or disadvantages of participating in the program will also be explored with a selected group of private providers.

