For the observations, content analysis will be used to conceptualize and classify events, behaviors and actions to obtain a rich understanding of quality of care and explanation of how women experience care at facilities [16]. Basic descriptive statistics will be calculated for key indicators from the record and register review. With regard to provider competence, descriptive analysis will identify competence areas that require strengthening. The data will be analyzed using inferential statistics to compare scores between levels of facilities and qualification and experience of providers. The data from exit interviews will be analyzed to describe use of evidence based practices by level of facility. Qualitative data derived from the in-depth interviews with mothers will be analyzed using the thematic Framework approach [17]. The obstetric referrals, indications for referral and details of referral-transport, costs, distance, and time will be described by the level of facility using mean, standard deviation and tests of significance. The referral pathways of the maternal deaths will be mapped on GIS and buffer analyzed. The buffer analysis will be used to study referring facility locations with regard to transfer time to CEmOC facilities.

3. Community level (mothers in the study villages):

At the community level we will collect primary data from recently delivered mothers to compare outcomes between eligible beneficiaries and non-beneficiaries (objective vii) for each of the programs. A cross-sectional study will be conducted with women residing in the selected study villages who delivered in the last year. JSY program participation is defined as an institutional delivery in any public health facility. Program non participation is defined as a home or private facility delivery. CY program participation is defined as a below poverty line (BPL) or tribal mother who delivers in a CY approved facility. Program non participation is defined as BPL or tribal mother who delivers outside of a CY approved facility.

Stratified systematic random sample will be used to select the study villages in each district. The districts will first be stratified by blocks (administrative units) and then the villages in each block will be classified into two strata based on the size of the population. Villages will be randomly selected from each strata based on the population proportion. Given the different design of each program, the sample sizes will vary in each province.

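### The primary outcome of the first cost-effectiveness approach, institutional delivery among matched participants, is 100% in both programs under the protocol's own definition of participation

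*Protocol article*

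**What the plan says.** All references are to the protocol article.

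- **Population.** Under Data collection methods, provincial level, objective iv: "The first approach will be to compare the costs and outcomes of the two programs for matched groups of participants".
- **Effect measure.** The next sentence reads: "The primary outcome will be the proportion of institutional delivery". Caesarean proportion, antenatal check-ups and delivery outcomes are listed as further outcomes. A second approach looks at equity within each system.
- **Participation.** It is defined only in the community-level section. For JSY: "JSY program participation is defined as an institutional delivery in any public health facility". For CY: "CY program participation is defined as a below poverty line (BPL) or tribal mother who delivers in a CY approved facility".
- **Institutional delivery.** The provincial-level text on the time series describes it as "institutional delivery (total number of women delivering in a public or private facility", so public and private facilities both count.
- **Type of economic analysis.** Objective (iv) in the Background plans a "sensitivity analysis by testing alternative assumptions for a cost utility analysis", and the Discussion again promises cost utility. The method text describes cost-effectiveness, names no utility measure, and says "we will not aim to comprise the analysis in a single index number".

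**The concern.** The population and the primary outcome of this approach do not fit together. The outcome asks whether a woman delivered in a facility, and belonging to the population already requires that she did. Such an outcome carries no information about either program.

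Promoting institutional delivery is the stated intended outcome of both programs, and the article says the evaluation is meant for policy makers and program managers. A primary effectiveness result that is equal by construction could be read as a finding that the programs are equally effective. The program with the lower payment would then look preferable for a reason unrelated to its performance.

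**Working it through.** The article gives no effect size, power or sample size for this comparison, so there is no figure to reproduce. The check sets the definitions side by side.

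**1. Outcome among participants.**
- JSY participant: delivered in a public facility. Public facilities count as institutional, so P(institutional | JSY participant) = 1.
- CY participant: BPL or tribal mother delivered in a CY approved facility. Table 1 describes these as empanelled private facilities, which also count, so P(institutional | CY participant) = 1.
- Difference: 1 − 1 = 0.
- Variance terms: 1 × (1 − 1) + 1 × (1 − 1) = 0.

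Matching cannot change this, because every possible member of either group has the same outcome.

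**2. What remains on the primary outcome.** The Table 1 payments illustrate it:
- CY: INR 288,000 / 100 = INR 2,880 per delivery.
- JSY: INR 1,400 (rural) or INR 1,000 (urban).
- Difference: 2,880 − 1,400 = INR 1,480, or 2,880 − 1,000 = INR 1,880.

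These are differences in program payment only. They are not full incremental costs: they leave out, for example, the state's cost of the public-facility delivery, transport and administration. They show only that a cost difference would be set against an effect difference fixed at zero.

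**3. The alternative matching.** Suppose the matched groups were participants and non-participants within a program, as in the propensity score analysis of objective vii. Let h be the share of non-participants who deliver in some facility. The difference is 1 − h. The participant side is still 100% by definition, so the contrast measures only where non-participants deliver.

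**4. All eligible mothers.** Let u be the share of eligible mothers who participate. Then P(institutional) = u × 1 + (1 − u) × h. This can vary between provinces whenever u and h are below 1. It equals 1 by necessity only when u = 1, which is the restriction that the current wording imposes. For orientation, Table 3 gives institutional delivery of 47% in Madhya Pradesh and 56% in Gujarat, a crude difference of 56 − 47 = 9 percentage points. That figure is unadjusted, refers to whole provinces and is confounded by province. It shows that the outcome can vary once non-participants are included; it does not estimate a program effect.

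**The case against.** The strongest reply is that the participation definitions stand under objective vii, where they separate users from non-users, and that objective iv does not define its participants. The choice of a proportion as outcome may suggest that a denominator including home births was intended. If so, the fault is an unstated denominator.

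This has some force, but it does not rescue the text. No other definition is given. The design of the programs leads to the same place, since JSY pays the mother on discharge and CY pays the obstetrician for deliveries. The article also distinguishes eligible women from those who participate when it defines uptake at the provincial level. If eligible women were meant, objective iv names the wrong group and needs the same correction.

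Some stronger inferences are tempting and are not supported:

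- **That the whole economic analysis can show no difference in effect.** Caesarean proportion, antenatal check-ups and birth outcomes can vary among participants, and the equity approach is separate.
- **That a promised cost-effectiveness ratio is undefined.** The method text promises no ratio and declines a single index.
- **That institutional delivery is lost from the evaluation.** It is studied over time under objective i, and place of delivery is modelled under objective viii.
- **That miscarriage must be dropped because the community survey samples women who delivered.** The article does not say that this outcome comes only from that survey.

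A condensed article may leave the choice of utility measure to the full protocol. The mismatch between cost utility and cost-effectiveness is therefore a point of wording and does not support the main point.

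**Conclusion.** The point holds for the primary outcome of the first cost-effectiveness approach. As written, that outcome is 100% in both programs, the difference is exactly zero, and the primary comparison reduces to cost. This rests on one assumption: that participants in objective iv means what it means in the community-level section, the only place where participation is defined. The defect lies in two stated elements that are incompatible, so it is not a detail left out of a condensed article. It is confined to this outcome in one of nine objectives, but there the text is wrong as written and needs correction. The inconsistency over cost utility is real, separate and minor.

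**What to change.** 1. **Change the denominator in objective iv.** Measure the primary outcome among all eligible mothers in the sampled villages, participants plus non-participants. The community survey already plans to record their place of delivery, costs and socio-demographic details.
2. **Make the provinces comparable.** Match or adjust between provinces on socio-demographic characteristics. JSY is open to all mothers and CY only to BPL or tribal mothers, so compare BPL/tribal mothers in both provinces at least as a sensitivity analysis.
3. **Limit the interpretation.** State that this between-province contrast is not by itself a program-attributable effect. The district time series of objective i should not be assumed to supply one for BPL/tribal mothers, because the article mentions no such breakdown.
4. **Keep the matched-participant comparison** for outcomes that can vary among participants, such as caesarean proportion, antenatal check-ups and birth outcomes.
5. **Separately, reconcile the wording.** Bring the cost-utility statements in objective (iv) of the Background and in the Discussion into line with the method text, or name the utility measure.

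The cost is a change of wording and denominator, with little or no new data collection apparent from the article. In return, the effect estimate will carry sampling uncertainty and confounding by province, and both should be reported.
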